### 1.22 Data management

De-identified data management will be performed by the Australian and New Zealand Intensive Care Research Centre (ANZIC-RC) located within the School of Epidemiology and Public Health of Monash University.

### 1.23 Protocol deviation

A protocol deviation is generally an unplanned excursion from the protocol that is not implemented or intended as a systematic change. The Chief investigator will be responsible for ensuring the study is conducted in accordance with the procedures and evaluations described in this protocol and will protect the rights, safety, and welfare of all subjects. The Chief investigator will not implement any deviation from, or changes of, the protocol, unless it is necessary to eliminate an immediate hazard to trial subjects.

For the purposes of this protocol, any deviations requiring notification to the Research Ethics Committee will be defined as any participant who

- Entered into the study even though they did not satisfy the entry criteria.
- Developed exclusion criteria during the study and not withdrawn.

When a deviation from the protocol is identified for an individual subject, the chief investigator will assess the deviation and the possible impact to the safety and /or efficacy of the subject to determine subject continuation in the study. If a deviation impacts the safety of a subject, the Chief investigator will inform the Research Ethics Committee in accordance with normal Hospital processes.

## **SAFETY CONSIDERATIONS**

### **1.24 Adverse Events and Other Safety Aspects**

Safety will be assessed throughout the study. As part of normal hospital care for all patients undergoing surgery at Austin Hospital, a complete baseline profile of each subject will be established by the treating surgical unit through medical history, clinical laboratory values, vital signs, physical assessments, and ECGs. During the course of the study, surgical and anaesthesia care, including vital signs, complete and targeted physical assessments, laboratory tests, and ECGs will be performed in accordance with normal hospital protocols. **There will be no deviation from standard care at any time point.**

All medical and surgical changes from baseline will be monitored throughout the study by the treating units and appropriate interventions will be taken accordingly.

The documentation of all adverse events specifically related to fluid intervention will begin at the time of first Trial Fluid administration and continue through to hospital discharge of all subjects involved in the study.

Data will be recorded in the CRF and will include a description of the event, date of onset, onset status (onset before/after the first dose of study medication), end of the event, severity, course of events, SAE, seriousness criteria, action with respect to study medication, treatment required, related to Trial Fluid and outcome of the event. AEs will be recorded and tabulated using the Common Terminology Criteria for Adverse Events (NCI-CTCAE) Version 4.0.

Severity of events will be determined by the Principal Investigators.

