### **1.25 Definition of Adverse Events**

An adverse event is defined as any untoward medical occurrence in a subject administered a study drug or has undergone study procedures and which does not necessarily have a causal relationship with this treatment. AE can therefore be any unfavourable and unintended sign (including an abnormal laboratory finding), symptom or disease temporally associated with the use of a medicinal (investigational) product, whether or not related to the medicinal (investigational) product.

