#### **Reporting of adverse events**

The study Investigators will notify Austin Hospital Research Ethics Unit and Baxter Healthcare on an expedited basis and no later than the time set forth in the named regulations for each report of any adverse reaction that is "serious" and "unexpected" (as defined below) and believed by Austin Hospital and/or

**The SPLIT Study: Saline (0.9%) vs. Plasma-Lyte® 148 Fluid Intervention  
Trial in Major Surgery Patients, Version 3, 1st Oct 2014**

the study Investigators to be causally associated with the use of the Study Materials.

A "serious adverse-reaction" is defined as any untoward medical occurrence that at any dose:

- (a) results in death;
- (b) is life threatening (i.e., the Study Subject was at immediate risk of death from the event as it occurred);
- (c) is a persistent or significant disability/incapacity;
- (d) requires inpatient hospitalization possibly related to the use of Study Materials;
- (e) prolongs hospitalisation;
- (f) is a congenital anomaly/birth defect; or
- (g) is an important medical event that jeopardizes the Study Subject and requires medical/surgical intervention to prevent one of the outcomes listed in this definition.

An "unexpected adverse reaction" is defined as an event that is not identified in nature, severity, or frequency in the current investigator brochure/package insert/product information.

The study investigators will notify each other of any events or concerns about the safety of the Study Subjects that arise as the Study progresses, even if these events or concerns do not meet the definition of an adverse event/adverse reaction requiring notification as described above.

The Study Investigators shall send an expedited copy of each suspected unexpected serious adverse reaction (SUSAR) simultaneously to Baxter Healthcare at the time the Study Investigators sends it to Austin Hospitals Research Ethics Unit. In addition, the Study Investigators shall make available to Baxter Healthcare promptly such records as may be necessary and pertinent to investigate any such SUSAR, if specifically requested by Baxter Healthcare.

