If a Baxter Healthcare product is used as part of the Study Materials, the Study Investigators shall notify Baxter Healthcare of all serious adverse events/adverse reactions (SAE) (including any pregnancy reports with or without an associated SAE) or other significant safety concerns (regardless of expectedness or causality) involving the Study Materials within 24 hours of awareness on a "CIOMS I" so that Baxter Healthcare may comply with worldwide regulatory authority reporting requirements related to the Baxter Healthcare product. The Study Investigators shall assist Baxter Healthcare in investigating any SAE and will provide any follow-up information requested by Baxter Healthcare.

Pregnancies shall be followed up by the Study Investigators to determine outcome (including premature termination) and status of mother and child and reported to Baxter Healthcare.

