### **Criteria for Causal Relationship of Trial Fluid**

**The SPLIT Study: Saline (0.9%) vs. Plasma-Lyte® 148 Fluid Intervention  
Trial in Major Surgery Patients, Version 3, 1st Oct 2014**

| Causal relationship to Trial Fluid | Criteria for causal relationship                                                                                                                                                                                                                         |
|-------------------------------------------|-----------------------------------------------------------------------------------------------------------------------------------------------------------------------------------------------------------------------------------------------------------------|
| Not Related                        | A clinical event, including laboratory test abnormality, with a temporal relationship to the Trial fluid which makes a causal relationship improbable, and/or in which other drugs, chemicals or underlying disease or surgery provides plausible explanations. |
| Possible                           | A clinical event, including laboratory test abnormality, with a reasonable time sequence to administration of the Trial fluid, but which could also be explained by concurrent disease, or other drugs or chemicals or surgery.                                 |
| Probable                           | A clinical event, including laboratory test abnormality, with a reasonable time sequence to administration of the Trial fluid, unlikely to be attributed to concurrent disease or other drugs or chemicals, or surgery.                                         |

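### Section 1.24 limits adverse event documentation to fluid-related events, against the protocol's own definition, serious-event rules and causality scale, so the recorded safety data would be incomplete and depend on attribution

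*Protocol*

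**What the plan says.** Section 1.24 of the protocol scopes the recording: "The documentation of all adverse events specifically related to fluid intervention will begin at the time of first Trial Fluid administration", continuing to hospital discharge. The same section lists the CRF items for each event. They include seriousness and "action with respect to study medication, treatment required, related to Trial Fluid and outcome of the event", and the events are to be tabulated by CTCAE grade.

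Section 1.25 defines an adverse event as an untoward occurrence "which does not necessarily have a causal relationship with this treatment", and repeats the point: "whether or not related to the medicinal (investigational) product".

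Under the subheading on reporting in 1.25 there are two separate duties. Expedited reporting covers serious, unexpected reactions believed by the hospital and/or "the study Investigators to be causally associated with the use of the Study Materials". The manufacturer, by contrast, must be told of all serious events and "other significant safety concerns (regardless of expectedness or causality) involving the Study Materials within 24 hours of awareness". Section 1.26 requires an SAE to go to the ethics unit within 24 hours and sets no causality condition.

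The causality table has three classes: Not Related, Possible and Probable. An event can be Not Related where "other drugs, chemicals or underlying disease or surgery provides plausible explanations".

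**The concern.** Two rules about which events are recorded cannot both govern the CRF. If site staff follow the opening sentence on documentation in 1.24, an event is recorded only once someone has attributed it to the fluid. If they follow the definition in 1.25, it is recorded first and attributed afterwards.

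The choice matters because safety is in the trial's title and objectives, and the Background and Rationale names adverse event incidence among the things this pilot is to supply for a pivotal trial. A count filtered by attribution is not an incidence. In a two-arm comparison the arms themselves supply the causal contrast, so individual attribution is not needed to detect an excess. It is also least reliable for the ordinary postoperative events in which a fluid effect might appear. A later analysis plan cannot repair this, since events that were never recorded cannot be recovered.

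**Working it through.** No figure in the protocol bears on this point, so the check sets the sections side by side and follows the possible kinds of event through them.

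1. **Non-serious event judged unrelated.** It is an adverse event under 1.25, lies outside the documentation scope in 1.24, and falls under no notification duty. Unless it also counts as a trial outcome, it appears nowhere.

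2. **Serious event judged unrelated.** It must be notified to the manufacturer under 1.25 and to the ethics unit under 1.26, on a separate SAE form. Whether it reaches the CRF is unclear. Section 1.26 sends to the adverse event page only those serious events that are also events of interest noted above, and the safety section contains no such list. The nearest antecedent is the fluid-related scope in 1.24. The event could therefore be notified and still be missing from the dataset used for tabulation.

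3. **Event, serious or not, judged possibly or probably related.** It is recorded under every reading.

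Two features show that the protocol presupposes wider recording than 1.24 states. The CRF has a field for relatedness, and the causality scale has a Not Related class. Both would be largely redundant if only related events were entered.

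The filter is also hard to apply consistently. Not Related may be chosen where disease or surgery plausibly explains the event. Possible applies where the timing is reasonable but disease, drugs or surgery could also explain it. A timely postoperative event can fit either class. Section 1.27 groups Possible with Probable as a relationship not excluded. Under 1.24 the choice between two overlapping classes could decide whether the event is recorded at all.

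Against this stand the harms that are captured regardless. Section 1.17.2 makes kidney injury or failure the primary outcome. Section 1.17.3 lists metabolic acidosis, acidemia, postoperative complications, renal replacement therapy, mechanical ventilation, ICU admission, and ICU and in-hospital death. None depends on relatedness, and section 1.30 compares binary outcomes by relative risk on an intention-to-treat basis. What remains exposed is adverse events and SAEs outside those outcomes. The protocol does not define postoperative complications, so how much that outcome absorbs is not known.

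The size cannot be computed. It would need the rate of adverse events or SAEs per arm and the share judged related, and the protocol gives neither.

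**The case against.** The strongest reply is that this is a wording conflict with little consequence. Section 1.24 does not say that only related events may be recorded, and its relatedness field fits recording relatedness as a descriptor. The duties in 1.25 and 1.26 stand on their own and are not limited by 1.24. The harms of most interest are compared as outcomes. Clinical staff are blinded (section 1.33), which limits differential attribution. Selective recording of non-serious events is defensible in a comparison of two standard fluids that section 1.19 regards as negligible risk and that relies largely on routine data. The detail of safety tables belongs in the analysis plan.

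Much of this stands. A reader might infer that the safety comparison loses most events, or that following 1.24 makes the SAE duties impossible to meet. The documents support neither. The outcomes in 1.17.2 and 1.17.3 carry no filter, the notification duties are independent of 1.24, and the Possible class covers many timely postoperative events that might otherwise be assumed to count as Not Related. Any numerical statement of lost events or lost precision would rest on invented rates.

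Three things do not fall away. Notification is not the same as entry in the trial dataset, and 1.26 leaves that link undefined. What is collected is a protocol matter, not one for the analysis plan. And under section 1.17 each fluid is given in its own period, so any drift in attribution between the two periods would fall along the treatment comparison even if blinding is perfect.

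**Conclusion.** The conflict is real and should be resolved. As written, the adverse event and SAE dataset would be incomplete and would depend on causality judgements, which weakens the incidence data the pilot promises. The effect is limited to events that are not already trial outcomes: mainly non-serious events judged unrelated, and unrelated SAEs that are notified but may not reach the CRF. No magnitude can be given. The conclusion rests on 1.24 being followed literally and on the events of interest in 1.26 having no wider meaning than the safety section supplies. It does not call the primary comparison into question.

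**What to change.** Reconcile sections 1.24 to 1.27 so that one rule governs recording:

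- Enter every SAE on the CRF from first trial fluid to hospital discharge, regardless of attribution, and replace the undefined reference to events of interest in 1.26 accordingly.
- Keep relatedness as a descriptor of a recorded event, not a condition for recording it. The overlap between Not Related and Possible then affects only a label.
- Tabulate SAEs by arm, with relatedness shown as a breakdown.
- If non-serious events are to stay limited to those suspected to be fluid-related, say so explicitly, so that the broad definition in 1.25 and the narrower recording rule no longer contradict each other.

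Investigators must already identify and report SAEs under 1.25 and 1.26, so the added cost is some CRF entry time and one more safety table.

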### **1.25 Definition of Adverse Events**

An adverse event is defined as any untoward medical occurrence in a subject administered a study drug or has undergone study procedures and which does not necessarily have a causal relationship with this treatment. AE can therefore be any unfavourable and unintended sign (including an abnormal laboratory finding), symptom or disease temporally associated with the use of a medicinal (investigational) product, whether or not related to the medicinal (investigational) product.

#### **Reporting of adverse events**

The study Investigators will notify Austin Hospital Research Ethics Unit and Baxter Healthcare on an expedited basis and no later than the time set forth in the named regulations for each report of any adverse reaction that is "serious" and "unexpected" (as defined below) and believed by Austin Hospital and/or

**The SPLIT Study: Saline (0.9%) vs. Plasma-Lyte® 148 Fluid Intervention  
Trial in Major Surgery Patients, Version 3, 1st Oct 2014**

the study Investigators to be causally associated with the use of the Study Materials.

A "serious adverse-reaction" is defined as any untoward medical occurrence that at any dose:

- (a) results in death;
- (b) is life threatening (i.e., the Study Subject was at immediate risk of death from the event as it occurred);
- (c) is a persistent or significant disability/incapacity;
- (d) requires inpatient hospitalization possibly related to the use of Study Materials;
- (e) prolongs hospitalisation;
- (f) is a congenital anomaly/birth defect; or
- (g) is an important medical event that jeopardizes the Study Subject and requires medical/surgical intervention to prevent one of the outcomes listed in this definition.

An "unexpected adverse reaction" is defined as an event that is not identified in nature, severity, or frequency in the current investigator brochure/package insert/product information.

The study investigators will notify each other of any events or concerns about the safety of the Study Subjects that arise as the Study progresses, even if these events or concerns do not meet the definition of an adverse event/adverse reaction requiring notification as described above.

The Study Investigators shall send an expedited copy of each suspected unexpected serious adverse reaction (SUSAR) simultaneously to Baxter Healthcare at the time the Study Investigators sends it to Austin Hospitals Research Ethics Unit. In addition, the Study Investigators shall make available to Baxter Healthcare promptly such records as may be necessary and pertinent to investigate any such SUSAR, if specifically requested by Baxter Healthcare.

If a Baxter Healthcare product is used as part of the Study Materials, the Study Investigators shall notify Baxter Healthcare of all serious adverse events/adverse reactions (SAE) (including any pregnancy reports with or without an associated SAE) or other significant safety concerns (regardless of expectedness or causality) involving the Study Materials within 24 hours of awareness on a "CIOMS I" so that Baxter Healthcare may comply with worldwide regulatory authority reporting requirements related to the Baxter Healthcare product. The Study Investigators shall assist Baxter Healthcare in investigating any SAE and will provide any follow-up information requested by Baxter Healthcare.

Pregnancies shall be followed up by the Study Investigators to determine outcome (including premature termination) and status of mother and child and reported to Baxter Healthcare.

### **1.26 Reporting of Severe Adverse Events**

In case of a SAE, the investigator will report the event to the Research Ethics Unit immediately (within 24 hours of awareness). The Chief investigator or delegate will complete and submit an SAE report form containing all information that is required on the form.

Reporting of a SAE to Baxter Healthcare does not relieve the Study Investigators of the responsibility for reporting it to the Austin Hospital Research Ethics Unit.

Any notification and reports required to be given to The Austin Hospital Research Ethics Unit, and to Baxter Healthcare and will be sent to:

Pharmacovigilance Manager  
Baxter Healthcare Pty Limited  
[contact]  
[contact]  
Email: [contact]  
Address: [name]

The Study Investigators shall ensure that the serious adverse event reporting and notification principles as agreed above are clearly reflected and described in this Protocol. In the event of any inconsistencies between the Protocol and the terms of this Agreement related to adverse event reporting, the terms of this Agreement shall prevail.

**Whilst this study is an interventional study on the basis of conventional Guidelines, it has many features that are more akin to an observational study than an interventional one. Specifically, the study involves no departure from standard care and does not involve the collection of any data that are not already being collected for clinical and / or quality assurance purposes.**

All of the events of interest noted above will be recorded on the CRF. Any situation involving these events of interest that also meets the criteria for an SAE will be recorded on the AE page of the CRF and marked 'serious'.

### **Criteria for Causal Relationship of Trial Fluid**

**The SPLIT Study: Saline (0.9%) vs. Plasma-Lyte® 148 Fluid Intervention  
Trial in Major Surgery Patients, Version 3, 1st Oct 2014**

| Causal relationship to Trial Fluid | Criteria for causal relationship                                                                                                                                                                                                                         |
|-------------------------------------------|-----------------------------------------------------------------------------------------------------------------------------------------------------------------------------------------------------------------------------------------------------------------|
| Not Related                        | A clinical event, including laboratory test abnormality, with a temporal relationship to the Trial fluid which makes a causal relationship improbable, and/or in which other drugs, chemicals or underlying disease or surgery provides plausible explanations. |
| Possible                           | A clinical event, including laboratory test abnormality, with a reasonable time sequence to administration of the Trial fluid, but which could also be explained by concurrent disease, or other drugs or chemicals or surgery.                                 |
| Probable                           | A clinical event, including laboratory test abnormality, with a reasonable time sequence to administration of the Trial fluid, unlikely to be attributed to concurrent disease or other drugs or chemicals, or surgery.                                         |

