### **1.17 Treatment allocation**

Patients will be randomly assigned, in alternating 6 weeks blocks to use either blinded Saline (0.9%) or Plasmalyte solution. There will be a three week wash-in period and a three-week wash-out period between each fluid intervention.

For example, assume:

**GROUP ONE:** Saline (Blinded)

**GROUP TWO:** Plasmalyte (Blinded)

Three weeks prior to commencement, blinded Saline will be introduced into all theatres, ICU and surgical wards for a 3 week wash-in period. **GROUP ONE** subjects will then receive Saline (blinded) for 6 weeks. This will be followed by a 3-week wash-out period of Saline (blinded). Plasmalyte solution (blinded) will then be washed-in for 3 weeks. **GROUP TWO** subjects will then receive Plasmalyte solution (blinded) for a 6 week period. Plasmalyte solution (blinded) will be washed-out for 3 weeks and the study will stop.

Total study duration: 24 weeks

Any patients who remain in hospital throughout the transition period will continue to receive the blinded fluid that they were originally assigned to for all postoperative crystalloid intervention. Thus blinded fluid will be made available as the only crystalloid fluid in all surgical wards and in the intensive care unit. No controls will be placed on the use of colloidal fluid therapy, blood products (red blood cells, platelets, cryoprecipitate or fresh frozen plasma, or any other fluid non-crystalloid fluid intervention e.g. dextrose, bicarbonate.

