### **1.27 Criteria for Causal Relationship to the Trial Fluid**

Adverse events that fall under either "Possible" or "Probable" will be defined as "adverse events whose relationship to the Trial Fluid could not be ruled out".

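### The causality table puts a well-timed event that surgery could explain in both Not Related and Possible, and section 1.27 draws its line between the two

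*Protocol*

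**What the plan says.** The table under Criteria for Causal Relationship of Trial Fluid has three classes. *Not Related* is an event with a timing "which makes a causal relationship improbable, and/or in which other drugs, chemicals or underlying disease or surgery provides plausible explanations". *Possible* is an event with a reasonable time sequence, "but which could also be explained by concurrent disease, or other drugs or chemicals or surgery". *Probable* is an event with a reasonable time sequence that is unlikely to be due to those other causes.

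Section 1.27 groups *Possible* and *Probable* as events "whose relationship to the Trial Fluid could not be ruled out". *Not Related* falls outside that group.

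Section 1.24 opens the recording rules with this sentence: "The documentation of all adverse events specifically related to fluid intervention will begin at the time of first Trial Fluid administration". It then lists the fields of the case report form (CRF). These include onset before or after the first dose, SAE status, seriousness criteria and relation to the trial fluid. It names the Principal Investigators as assessors of severity and names nobody for causality. Section 1.25 defines an adverse event as an occurrence "which does not necessarily have a causal relationship with this treatment".

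Under Reporting of adverse events, expedited notification applies to serious, unexpected reactions that are believed to be causally associated with the study materials. Separately, serious adverse events go to the manufacturer whatever their expectedness or cause. Section 1.26 sends them to the ethics unit within 24 hours with no causality condition.

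**The concern.** A causality scale should give each event one class. Here two classes share the same ground, and section 1.27 places its boundary exactly between them.

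The shared ground is unlikely to be empty. By section 1.13 every participant has surgery with an overnight stay, so surgery is often available as another explanation. Section 1.17 says: "Thus blinded fluid will be made available as the only crystalloid fluid in all surgical wards and in the intensive care unit". Section 1.16 allows open-label fluid only in rare situations. Many postoperative events will therefore follow trial fluid in a reasonable time sequence.

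Three things rest on the label or on the judgement behind it: the CRF field on relation to the trial fluid, the class defined in section 1.27, and the belief in causality that triggers expedited notification. Safety is part of the overall objective under Objectives, and the Background names adverse event incidence among the information the pilot is to supply for a later trial.

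**Working it through.** The protocol states no figure on this point, so there is none to reproduce. The check is logical.

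**Inputs.** All come from the causality table. T = the time sequence is reasonable. A = surgery, disease, drugs or chemicals give a plausible alternative explanation.

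- *Not Related*: not T, **or** A. The conjunction in the table is inclusive, so either limb is enough.
- *Possible*: T **and** A.
- *Probable*: T **and** not A.

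**Result as written.**

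| T | A | Classes met | Counted by section 1.27? |
|---|---|---|---|
| yes | yes | *Not Related* and *Possible* | no and yes |
| yes | no | *Probable* | yes |
| no | yes | *Not Related* | no |
| no | no | *Not Related* | no |

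One of the four cells carries two labels. It is the cell of a well-timed event that surgery or disease could explain. Section 1.27 counts that event under one label and leaves it out under the other. Nothing in the protocol says which label takes precedence.

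**Size.** Let k be the number of events that are clearly related and m the number in the doubly labelled cell. For identical events the count under section 1.27 can lie anywhere from k to k + m. The protocol gives neither k nor m, so the width of that range is unknown. Any percentage would only return the rate assumed for m.

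**Possible repairs, tested in the same way.**

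- Replacing the conjunction with a plain *and* makes *Not Related* equal to (not T and A). The overlap goes, but the cell with T no and A no is left without a class.
- Limiting *Not Related* to not T gives exactly one class in all four cells.
- Adding a clearly established other cause as a second ground for *Not Related* keeps the classes separate, provided that the *Possible* row is reserved for well-timed events in which a contribution of the fluid cannot be excluded.

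**The case against.** **The two wordings might set different thresholds.** An explanation that the *Not Related* row calls plausible could be meant as stronger than one that merely could apply. The protocol defines no such threshold, and a plausible explanation is one that could explain the event. This does not remove the overlap.

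**No analysis of fluid-related events is planned.** Section 1.27 only defines a class. The outcome sections and section 1.30 list no such comparison, the tabulation in section 1.24 is by CTCAE, and the Background speaks of adverse events, not related ones. This stands. A reader might infer that a planned safety table is spoiled; the protocol does not contain that table.

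**Recording may not depend on the label.** From the opening sentence of section 1.24 a reader might infer that an ambiguous event can go unrecorded. The CRF fields listed next include relation to the trial fluid and onset before the first dose. Those fields make little sense if only events already judged related are entered, and they suggest that relatedness is assessed on recorded events. The sentence is loose, but it does not establish a filter.

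**Serious events may all reach the CRF.** Section 1.26 says: "Any situation involving these events of interest that also meets the criteria for an SAE will be recorded on the AE page". The safety sections give no list of such events, so a reader might infer that some serious events never enter the CRF. Section 1.24 lists SAE status and seriousness criteria as CRF fields, which weakens that reading. Section 1.26 also defers to an agreement on adverse event reporting that is not shown, so the question cannot be settled from the protocol.

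**Clinical staff are blinded.** Section 1.33 covers all clinical staff involved in care, so the ambiguity need not favour either fluid. This stands.

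**Conclusion.** The overlap is certain on the text. A well-timed event with a plausible surgical, disease or drug explanation meets both *Not Related* and *Possible*, and section 1.27 gives those labels opposite consequences. This is a stated rule that contradicts itself, not a detail left to an analysis plan.

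The consequence is small. It reaches the CRF field on relatedness, the class in section 1.27 and the causality judgement behind expedited notification. That assumes assessors use this table for all three, which is reasonable because the protocol gives no other causality criteria. How often the double label would arise cannot be quantified.

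A reader might go further and infer bias between the fluids or a threat to the main results. The documents support neither. The primary and secondary outcomes in sections 1.17.2 and 1.17.3 carry no causality condition, and notification of serious adverse events to the manufacturer applies "regardless of expectedness or causality) involving the Study Materials within 24 hours of awareness". The point is worth correcting because correction is cheap, not because the trial's conclusions depend on it.

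**What to change.** In the causality table, replace the *Not Related* clause that follows the conjunction. *Not Related* should apply only when the timing makes causation improbable or when another cause is clearly established. State in the *Possible* row that a well-timed event which surgery, disease or drugs could also explain is *Possible* whenever a contribution of the fluid cannot be excluded. Leave the *Probable* row as it is.

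As a minor clarification, reword the opening sentence on documentation in section 1.24. Relatedness should be assessed on recorded events and should not be a condition for recording serious adverse events.

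The cost is one rewritten clause, one added statement and one reworded sentence. All serious events must already be notified, so none has to be newly sought; at most they need CRF entry. The drawback is that the fluid-related count becomes somewhat larger and less specific. Some judgement also remains, because deciding that another cause is clearly established, or that the fluid is excluded, is still up to the assessor.
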